## Abstract

Early prevention and treatment of metabolic syndrome (MetS) through healthy eating and physical activity are essential for reducing chronic disease risk among youth. The school food and physical activity environment significantly influences children's health behaviors. Yet, interventions targeting schools' health environments are sparse, and none empower middle school students to be change agents. We describe the process and rationale for evaluating Strong Teens for Healthy Schools (STHS), a multilevel middle school civic engagement program promoting healthier school environments through student-driven projects. We will test the efficacy of STHS for reducing MetS risk and improving positive youth development outcomes among students at middle schools where >40% of students identify as Black/African American or Hispanic/Latino (*n* = 20 schools; *n* = 20–25 students per school) through a pilot cluster randomized controlled trial. Schools randomized to STHS intervention will participate in 16 modules on civic engagement, healthy eating, and physical activity, and schools randomized to the delayed intervention group will receive the curriculum one year later. Student outcomes will be measured at four points: within 1 month of recruitment, at end of intervention, at start of next school year, and at end of next school year. Secondary outcomes include students' perceptions of peers' health behaviors and environmental assessments through photovoice. Evaluating the efficacy of STHS in improving MetS and promoting positive youth development will provide initial evidence on improving physical activity and nutrition outcomes at individual, social, and environmental levels, paving the way for larger-scale studies and informing dissemination efforts.

**Clinical Trial Registry Number:**
ClinicalTrials.gov ID NCT05867433.

## Introduction

Metabolic syndrome (MetS) is a cluster of risk factors that increases an individual's risk for cardiovascular disease and type 2 diabetes (1). These risk factors can appear early in childhood, leading to lifelong chronic disease morbidity and mortality (2, 3). A diagnosis of pediatric MetS, following the International Diabetes Federation (IDF) criteria and modified to meet appropriate pediatric thresholds, requires the presence of abdominal obesity plus at least two of the following risk factors: hyperglycemia or insulin resistance, hypertension, elevated triglycerides, or low levels of high-density lipoprotein (4). In the United States, MetS risk factors are increasingly evident earlier in life and affect races and ethnicities disproportionately (5, 6). Among adolescents aged 12 to 19 years, 10.1% have MetS, and 73.2% have at least one condition related to MetS (5). Among overweight adolescents, one in three is affected by MetS (7). Cardiometabolic risk factors, such as obesity and type 2 diabetes, are more prevalent among adolescents who identify as African American/Black and Hispanic/Latino compared to their White counterparts (8).

Early prevention and treatment of MetS, through the promotion of healthy lifestyle behaviors, is essential for reducing the incidence of cardiovascular disease and type 2 diabetes throughout life (9, 10). Diet quality and physical activity are two healthy lifestyle behaviors closely linked to MetS (11). However, among adolescents, 66% exhibit poor diet quality, and only 8% meet the recommended 60 min of physical activity per day, with a smaller proportion of African American/Black and Hispanic/Latino adolescents adhering to dietary and physical activity recommendations (12, 13). Interventions that promote physical activity and healthy eating behaviors are needed to reduce MetS and improve the health of children and adolescents.

In the U.S., >50 million youth spend half of their waking hours and consume half of their meals at school, making it an ideal setting for diet and physical activity interventions (14). Prior studies have shown that changes to the middle school food and physical activity environment have a strong, positive impact on children's dietary and physical activity behaviors and weight outcomes (15–18). As established by ecological systems theory, health-related behaviors occur within a dynamic system where surrounding environments can encourage, discourage, or prohibit behaviors (19). The school food and physical activity environment has a major impact on children's health behaviors and certain MetS conditions, such as adiposity, making it essential for school health environments to promote healthy eating and physical activity to prevent and treat MetS (17, 20).

A growing body of research demonstrates the potential of youth civic engagement activities to catalyze environmental change and create positive health environments, which can also lead to positive youth development outcomes (e.g., competence, confidence, connection, character, and caring) (21). Positive youth development, in turn, promotes prosocial behaviors by engaging youth in their community and can enhance resilience, self-esteem, and academic success (22, 23). Additionally, civic engagement in this developmental stage is positively linked to future income and educational attainment in adulthood—two critical social determinants that influence MetS conditions and lifelong health (22, 24, 25). Despite the many benefits, few youth civic engagement interventions that focus on nutrition or physical activity are documented in the literature, and none have been implemented or rigorously evaluated in a middle school setting (26–28).

As a result, we adapted Strong Teens for Healthy Schools (STHS)—a multilevel middle school civic engagement program that promotes healthier school environments through student-driven projects—from Change Club. Change Club, a 24-week (two times per week) evidence-based civic engagement program, aims to improve health behaviors and outcomes among adults in underserved communities by guiding individuals to create healthy environmental changes within their communities (29). For Change Club, mechanisms of changing physical activity and healthy eating behaviors were focused on social cognitive theory constructs at the individual level and influencing multiple environments within a socioecological framework (e.g., social support). The STHS program provides group-based physical activity and nutrition education to promote healthy behaviors and reduce MetS risk.

The purpose of this manuscript is to describe the process and rationale for developing STHS, as well as the design of pilot cluster randomized controlled trial used to test the efficacy of STHS for: (1) reducing MetS syndrome risk, and (2) improving positive youth development outcomes among middle school student at schools where >40% of the student body identifies as Black/African American or Hispanic/Latino. We chose to recruit schools with a high prevalence of Black/African American or Hispanic/Latino students due to the disparities in cardiometabolic risk factors, coupled with lower engagement in healthy eating and physical activity than their White counterparts, as described above (12, 13). Additionally, we describe processes for assessing the impact of STHS in changing perceived health-related behaviors among the peers of STHS participants (social level) and the school health environment (environmental level).

## Methods and analysis

### Design

We will recruit two cohorts of schools (*n* = 20 schools, total) to participate in a 9-month pilot cluster randomized controlled trial. The study design processes—including school recruitment, enrollment, and randomization, as well as student recruitment, data collection timepoint, and program participation—are illustrated in Figure 1 and described in detail below. Once a school agrees to participate, it will be randomized to receive the STHS intervention immediately or a delayed intervention condition (i.e., control group). The delayed intervention group will receive the curriculum to implement at their discretion, one school year after serving as a control. We will collect pre-(beginning of the academic year; T1) and post-test outcomes (end of the academic year; T2) for intervention and delayed intervention conditions. Additionally, for the intervention group, we will gather outcomes at 4 months (T3) and 12 months (T4) post-intervention to assess the short- and long-term maintenance of the intervention effects. The trial has been registered on clinicaltrials.gov (NCT05867433). The Institutional Review Board at Texas A&M University approved all measures, procedures, and protocols (IRB2023-0530D).

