#### Delayed intervention control group

The delayed intervention control group will continue with usual care during the first school year, as they will not be asked to add or remove any of their current physical activity, healthy eating, or positive youth development programming. During that year, students will be recruited to take part in data collection within 1 month of the student recruitment period (T1) and at the end of the school year (T2). After T1 and T2 data collection is complete, the control schools will receive the STHS intervention and $3,000, as described below, to implement at their discretion.

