### Measures

All student participant outcomes will be measured for student participants at both the intervention and delayed intervention control group schools within 1 month of the student recruitment period (T1), at the end of the school year or intervention period (T2), at the start of the next school year (T3), and at the end of the next school year (T4; Figure 1). Data collection sessions are estimated to take 45 minutes per student, and measures will be administered to students as a group. The two primary individual-level outcomes for this study are changes in MetS and positive youth development. Secondary individual-level outcomes include: (1) individual metabolic risk factors (blood pressure, fasting blood glucose, waist circumference, HDL cholesterol, and triglycerides); (2) body mass index percentile; (3) fruit and vegetable consumption; (4) accelerometer-derived physical activity, sedentary time, and sleep; and (5) cardiorespiratory fitness. Finally, other outcomes we will survey include TPB constructs related to nutrition and physical activity, nutrition- and physical activity-related behaviors, and youth's engagement with the school health environment. At the social level, we will assess students' perceptions of their peers' physical activity and healthy eating. At the environmental level, we will: (1) measure students' perceptions of the school health environment; (2) have school administration and staff complete a school environment assessment; and (3) conduct photovoice sessions. Student participants in both the intervention and the delayed intervention control group will receive a $50 gift card for each data collection session they complete (T1 to T4; $200 maximum for completing all sessions).

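### The Design section measures T3 and T4 in the intervention arm only, while the Measures section measures both arms; the choice decides whether the maintenance result has a control group

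*Protocol article*

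**What the plan says.** All places are in the protocol article.

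- **Design, first two visits.** "We will collect pre-(beginning of the academic year; T1) and post-test outcomes (end of the academic year; T2) for intervention and delayed intervention conditions".
- **Design, later visits.** The next sentence adds that "for the intervention group, we will gather outcomes at 4 months (T3) and 12 months (T4) post-intervention", and gives the purpose: "to assess the short- and long-term maintenance of the intervention effects".
- **Measures, arms.** "All student participant outcomes will be measured for student participants at both the intervention and delayed intervention control group schools". The four visits are then listed; the last two fall "at the start of the next school year (T3), and at the end of the next school year (T4; Figure 1").
- **Measures, payment.** "Student participants in both the intervention and the delayed intervention control group will receive a $50 gift card for each data collection session they complete", with the limit given as "T1 to T4; $200 maximum for completing all sessions".
- **Delayed intervention control group.** This section describes the first school year and names T1 and T2 within it. It then says: "After T1 and T2 data collection is complete, the control schools will receive the STHS intervention", together with $3,000, for use at the school's discretion.
- **Abstract and Recruitment.** The Abstract gives four measurement points without separating the arms. Recruitment limits eighth-grade enrolment so that students can be followed up, again without separating the arms.
- **Quantitative analysis.** The stated between-group test is for post-intervention outcomes adjusted for baseline. It does not say which arms enter at T3 or T4.

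**The concern.** Which arm attends which visit is a fact of data collection, and the article states it in two incompatible ways. A later analysis plan cannot repair this, because control data not collected at T3 cannot be recovered.

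The two versions also answer different questions. Without controls at T3 and T4, maintenance can only be read from change within the treated arm. These are fifth- to eighth-graders, and outcomes such as waist circumference and blood pressure move with growth. T3 also falls at a different point in the school year from T2. One arm alone cannot separate those influences from a lasting programme effect. With controls at both visits, T3 gives a between-arm estimate. T4 needs more careful wording, because control schools will by then have had the curriculum and the money for most of a school year.

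**Working it through.** **1. Visits by arm, as each section states them**

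| Section | Intervention | Control |
|---|---|---|
| Design | T1, T2, T3, T4 | T1, T2 |
| Measures | T1, T2, T3, T4 | T1, T2, T3, T4 |
| Delayed intervention control group | not covered | T1, T2 in the first year; silent on T3 and T4 |
| Abstract | four points, arms not separated | four points, arms not separated |

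The direct conflict is between Design and Measures.

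**2. Check against the gift-card maximum (Measures)**

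Maximum = sessions × $50.

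- Four sessions: 4 × $50 = $200, which reproduces the stated figure, and it is stated for both arms.
- Two sessions, as Design implies for controls: 2 × $50 = $100, which does not match.

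So the Measures schedule is costed for control students and is not just loose phrasing.

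**3. Number of control schools**

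Randomization uses two blocks of ten schools at 1:1, so 2 × 5 = 10 control schools. Under Design, 0 of 10 contribute at T3 or T4, and no between-arm effect can be estimated there.

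**4. Control exposure if both arms are measured**

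- *T3.* Control schools receive the programme once T2, at the end of the school year, is complete. T3 is at the start of the next school year. The curriculum is 16 one-hour modules, delivered when the school chooses. Little of it is likely to have been delivered by T3.
- *T4.* This is the end of that next school year. Any number from 0 to 10 of the 10 control schools may have delivered the programme; the documents give no uptake figure.

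**5. What dilution at T4 could look like (illustration only)**

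Assume the intervention arm keeps the full planning effect, d = 0.27 (Sample size), and controls have gained a share f of it by T4. The value of f is an assumption, so the whole range is shown. Expected contrast = 0.27 × (1 − f).

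| f | Expected d at T4 |
|---|---|
| 0 | 0.27 |
| 0.25 | 0.2025 |
| 0.5 | 0.135 |
| 0.75 | 0.0675 |
| 1 | 0 |

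A small T4 contrast could therefore mean either that the effect faded or that controls caught up. This table shows why T4 needs its own description; it is not evidence for the contradiction.

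**6. Gift-card cost if Design is the operative schedule**

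- One added control visit: 10 schools × 20 to 25 students × $50 = $10,000 to $12,500.
- Both T3 and T4: 2 × that = $20,000 to $25,000.

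**The case against.** The strongest reply is that this is one loose sentence in Design. The Abstract, Recruitment and Measures all fit follow-up in both arms, and Figure 1, which is not shown, may display the intended schedule. That is a good reason to think Measures is the real plan. It does not remove the conflict, since a figure cannot make two opposed sentences agree.

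A second reply is that giving controls the programme after T2 is a disclosed trade-off. The Discussion says school staff and Extension agents had ethical concerns about withholding it. This stands: later control exposure belongs to the design and is not an error. It affects only how T4 is described.

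A third is that the article nowhere says within-arm change at T3 and T4 will be read as a causal effect, and that the follow-up model may sit in an analysis plan not shown. This is also fair, and the absence of a T3/T4 model is not raised here. The stated purpose does, however, refer to maintenance of intervention effects, which one-arm data cannot isolate.

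Three stronger readings are tempting, and the documents do not support them:

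- *That the control-group section confines controls to T1 and T2.* It describes the first school year and does not mention T3 or T4. It is evidence on when controls receive the programme, not on the visit conflict.
- *That maintenance is compromised whichever section is followed.* Under Measures, T3 can be largely uncontaminated.
- *That T4 is no longer a randomised comparison.* Compared as allocated, it still is. The question changes to immediate versus delayed offer.

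**Conclusion.** The contradiction holds, and it lies between Design and Measures. Following Design leaves the maintenance result as an uncontrolled before-after change in growing adolescents. Following Measures keeps a usable randomised contrast at T3 and an interpretable, though possibly diluted, one at T4.

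The severity is moderate. The primary T1–T2 comparison uses visits on which all sections agree, and what is at risk is follow-up in a pilot trial.

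The conclusion rests on two assumptions. The first is that handover follows directly after T2, as the control-group section says. Design's phrase about one school year could be read as a later handover, which would reduce exposure at T4. The second is that few control schools start before T3. That is plausible from the timing but not guaranteed, because delivery is at their discretion. Exposure at T4 is unknown, and the ceiling of 10 of 10 schools is a logical limit, not an estimate.

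**What to change.** 1. Correct the Design section so that T3 and T4 are collected in both arms, as Measures already schedules and pays for. Add a sentence to the control-group section saying that control students continue to T3 and T4.
2. Analyse T3 as a between-arm comparison with the same baseline-adjusted model used at T2, with the T3 score as the outcome.
3. Record the date on which each control school starts the programme, and report any that start before T3.
4. Keep the as-allocated comparison at T4, described as immediate versus delayed offer of the programme and not as maintenance against untreated controls.

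If Measures is the operative plan, the cost is wording plus a log of start dates. If Design is operative, control visits must be added at 10 schools. The gift cards come to about $10,000–12,500 for T3 alone, or $20,000–25,000 for T3 and T4, plus staff time. If only one visit can be afforded, T3 is the one to keep, because its contrast is the cleaner of the two.

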**Figure 1 F1:**
[figure not shown]
Study design and program implementation for cluster-randomized controlled trial to evaluate the strong teens for healthy schools program..

#### Study setting

The study will take place in Texas, United States (US). Texas is the second most populous state in the country (30.5 million residents in 2023) and had the highest population increase of any state (473,000 new residents) in 2023 (14). Among Texas residents, 13.6% identify as non-Hispanic Black/African American, 39.8% as Hispanic/Latino, and 76.8% as White (14). Although state-level prevalence of MetS is not available, 21.5% of children 10–17 years old have obesity in Texas, one of the highest prevalences in the nation, stressing the importance of programs addressing MetS in this state (30). Furthermore, obesity rates are nearly twice as high for African American (26%) and Hispanic (29%) children as for Non-Hispanic White children (17%) (31).

The STHS program will be implemented in partnership with Texas A&M AgriLife Extension agents (32). Texas A&M AgriLife Extension is an education agency that provides programs, tools, and resources on a local and statewide level (33). AgriLife Extension has 250 offices (one in almost every Texas county), 900 extension educators, and a network of almost 100,000 volunteers that support the delivery of programs (33–35). Extension agents within the Family and Community Health and 4-H Youth Development units aim to help Texans better their lives through science-based educational programs designed to improve the overall health and wellness of individuals, families, and communities (36, 37). Agents deliver programs in the local communities (e.g., worksites, recreation centers, community events, military bases), as well as within local schools (36, 37).

#### Study eligibility

The inclusion criterion for schools is that >40% of the student body identifies as Black/African American or Hispanic/Latino. With regards to students, all students at a school that is randomized to receive STHS can participate in STHS and are not required to participate in study-related activities. For students who participate in study-related activities, the inclusion criteria are being in the fifth through eighth grades and enrolled at a middle school receiving STHS or the control condition. The exclusion criteria for students who participate in study-related activities are participation in a weight loss program in the past 3 months or the presence of a condition that prevents participation in physical activity.

### Selection of subjects

#### Recruitment

School recruitment will occur using a two-pronged approach. First, we will use the Texas Education Agency website to identify contact information for all middle schools in Texas that meet inclusion criteria (38). We will recruit schools using emails, phone calls, and information folders dropped off at eligible schools in Texas. Simultaneously, we will work with AgriLife Extension Family and Community Health and 4-H agents to identify schools that may be interested in participating in the study. We will hold in-person or virtual meetings with school representatives (e.g., school health advisory councils) to provide an in-depth program description. School administrators from all schools that enroll in the study will sign a memorandum of understanding (MOU) agreeing to participate.

Within schools, we will recruit 5th through 8th grade students (*n* = 20–25 students per school). Eighth-grade students will only be recruited in schools that also have an attached high school where eighth-grade students matriculate, so that they can be assessed at follow-up. Otherwise, we will not recruit 8th-grade students because their transition into high school could introduce new individual and/or environmental factors that may affect study outcomes. Likewise, we will only recruit 5th through 8th grade students from elementary schools if the grade does not matriculate into another school the following year. We will disseminate information for participating in the STHS program via school-wide announcements, flyers posted at the intervention schools, and school-sponsored events. Students and their parents will also receive an email with information about participating in the research study and information on how to contact the research team if they are interested in their student(s) participating. We will also host information sessions for parents and students before and after school, where they can ask more questions about the program. Prior to signing consent forms, the research team will screen participants for inclusion and exclusion criteria. If the student qualifies for the study, the parent will be asked to read and return a consent form. Students will be asked to assent to participate in all study procedures.

